## Abstract

**Background:**

Gastric Cancer (GC) is the fourth most deadly cancer worldwide. Enhanced understanding of its key epidemiological and molecular drivers is urgently needed to lower the incidence and improve outcomes. Furthermore, tumor biology in European (EU) and Latin American (LATAM) countries is understudied. The LEGACy study is a Horizon 2020 funded multi-institutional research approach to 1) detail the epidemiological features including risk factors of GC in current time and 2) develop cost-effective methods to identify and integrate biological biomarkers needed to guide diagnostic and therapeutic approaches with the aim of filling the knowledge gap on GC in these areas.

**Methods:**

This observational study has three parts that are conducted in parallel during 2019–2023 across recruiting centers from four EU and four LATAM countries: Part 1) A case-control study (800 cases and 800 controls) using questionnaires on candidate risk factors for GC, which will be correlated with clinical, demographic and epidemiological parameters. Part 2) A case-control tissue sampling study (400 cases and 400 controls) using proteome, genome, microbiome and immune analyses to characterize advanced (stage III and IV) GC. Patients in this part of the study will be followed over time to observe clinical outcomes. The first half of samples will be used as training cohort to identify the most relevant risk factors and biomarkers, which will be selected to propose cost-effective diagnostic and predictive methods that will be validated with the second half of samples. Part 3) An educational study, as part of our prevention strategy (subjects recruited from the general public) to test and disseminate knowledge on GC risk factors and symptoms by a questionnaire and informative video. Patients could be recruited for more than one of the three LEGACy studies.

**Discussion:**

The LEGACy study aims to generate novel, in-depth knowledge on the tumor biological characteristics through integrating epidemiological, multi-omics and clinical data from GC patients at an EU-LATAM partnership. During the study, cost-effective panels with potential use in clinical decision making will be developed and validated.

**Trial registration:**

ClinicalTrials.gov Identifiers:

Part 1: NCT03957031.

Part 2: NCT04015466.

Part 3: NCT04019808.

**Supplementary Information:**

The online version contains supplementary material available at 10.1186/s12885-022-09689-9.

## Background

Gastric Cancer (GC) is the fifth most common and fourth most deadly cancer worldwide [1]. Risk factors associated with the development of GC include *H. pylori (HP)* infection, unhealthy lifestyle habits including obesity, smoking, consumption of alcohol and processed meat. Other risk factors associated with the development of GC include atrophic gastritis, partial gastrectomy, and inherited genetic predisposition [2]. Patients with GC report a variety of symptoms including indigestion, abdominal pain, changes in bowel movement habits, weight loss and fatigue. However, symptoms are often hard to interpret and in over half of cases tumors have already metastasized to regional lymph nodes or distant locations by the time they are recognized. At this advanced stage of the disease, systemic treatment is only limited effective and associated with a median overall survival of 11 months [3, 4].

Furthermore, geographic variation in the incidence of GC have been reported. The global burden of gastric cancer is ﻿over 1,000,000 new cases and 769,000 deaths per year. Gastric cancer age standardized incidence rates are highest in Eastern Asia with rates of 32.5 for males and 13.2 for females. Most extensive studies have been performed on Northern American and Asian populations, which have led to better prevention and screening strategies. For example in Japan 2/3 of the incidence rates are early stage cancers, leading to declining dead rates [5]. Also in other parts of the world such as South America and Eastern and Southern Europe gastric cancer is a prevalent disease. However, these populations are often underrepresented in molecular profiling studies and clinical trials and therefore not completely understood [1]. Geographic variations in incidence rates are seen between but also within continents [6]. This could be illustrated by the differences in mortality in Chile and its neighboring country Argentina: The number one cancer death cause for Chilean males is GC, while for males in Argentina, GC is ranked in the fifth place. For females from these countries an opposite trend is observed. Several studies have suggested there may be a strong environmental component explaining these regional variations in GC incidence and mortality, as well as in age, obesity and lifestyle [6–8]. However, direct comparisons in risk factors between countries is challenging as most of this knowledge comes from patient data included in different studies [9, 10]. Great geographical differences may also be explained by differences that are observed in prevalence and resistance rates of HP, which infects 50% of the world population and is the most important risk factor of GC [11, 12]. Furthermore, epidemiological and molecular features of GC vary widely by histological type, location, and genetic makeup of the tumor among patients worldwide [13].

There have been multiple attempts to increase our understanding of the molecular drivers of GC [14, 15]. Studies from The Cancer Genome Atlas (TCGA) project and The International Cancer Genome Consortium (ICGC), for instance, have identified four molecular subgroups based on genomic, epigenetic, transcriptomic and proteomic data: tumors positive for Epstein-Barr virus, microsatellite instable tumors, genome stable cancers and tumors with chromosomal instability [14, 16]. These subgroups differ in molecular and immunological features [17], which are associated with prognosis and response to treatment [18–20]. TCGA profiling has mostly been via analysis of non-advanced gastrectomy samples (stages I-II). Much less is known about the molecular profile of advanced cancers (stage III-IV) and cancers located at the gastroesophageal junction (GEJ). Furthermore, as patients from European (EU) and Latin American (LATAM) countries are underrepresented in these studies, it is unknown whether the molecular subtypes are fully representative of these populations [21]. Finally, available multi-omic classification procedures are too difficult and expensive to be implemented in the clinical setting, especially in LATAM countries.

All together these studies showed that a better understanding of the key oncogenic drivers and epidemiological factors are needed in GC from European and LATAM countries to improve GC prevention therapeutic approaches. To accomplish this goal we have set up the LEGACy study: a consortium between 11 research institutes from European and Latin American countries with the goal to 1) identify and comparing GC characteristics and associated risk factors between GC patients and healthy controls in EU and LATAM populations due to identify high-risk groups with a view to tailoring early detection and diagnosis; 2) increase our understanding of advanced GC tumor biology in EU-LATAM from a multi-omics approach that will provide extensive information including the tumor’s pathologic, genetic, immunologic and microbiome characteristics. This could lead to clinically relevant diagnostic or prognostic biomarkers and potential targets for therapy; 3) prevention by measuring and educate the general population on GC risk factors and symptoms and promoting healthy lifestyle habits with the ultimate goals to improve GC outcomes. Understanding the regional variations in biological and clinical behavior of GC will help to create a foundation for globally implementable diagnostic and treatment approaches.

## Methods/design

### Patients

Patients with GC and GEJ cancer will be recruited from eight university medical centers in seven different countries in EU (Spain, Netherlands, and Portugal) and LATAM (Argentina, Mexico, Chile, and Paraguay) from 2019 to 2023. Advanced stages will include state III and IV according to the American Joint Committee on Cancer (AJCC) stage system, GEJ will include Siewert type I and II tumors [22]. The clinical sites were selected based on their interest, expertise and geographical location, as well as the recruitment potential for the purpose of this study. Patient recruitment for each study is performed by coordinating a multidisciplinary team in each center including gastroenterologists, pathologists, surgeons, and medical oncologists. All patients should go through the informed consent procedure approved by each Institutional Research Board to participate in each of the sub studies.

### Institutions and partners

LEGACy is a multi-institutional research approach performed by a team of four LATAM and seven EU organizations. The study members and centers can be found in Fig. 1 and in Supplementary Table 1. To ensure homogeneity and reproducibility of data collection by all different project partners the recruitment of subjects and the collection and handling of patient material and data has been standardized via use of a laboratory handbook. This handbook provides standard operating procedures on all processes and procedures pertaining to subjects, samples and assays included in the LEGACy project. All researchers, doctors, nurses, and data managers receive training on correct questionnaire administration, clinical data collection and biopsy collection before they begin work in the project.

**Fig. 1 Fig1:**
[figure not shown]
Overview LEGACy; Indicating which centers contribute to which determination and related parts of the project. ANAX: Anaxomics SL (Spain); ECPC: European Cancer Patient Coalition (Belgium); GENPAT: Genpat SL (Paraguay); IAF: Institute Alexandre Fleming (Argentine); INCAN: Caner Insitute of Mexico (Mexico); INCLIVA: Biomedical Research Center INCLIVA (Spain); PUC: Pontificia University of Chile (Chile); ULEI: University of Leipzig (Germany); VHIO: Valld’Hebrón Insitut of Oncology (Spain); VUMC: Amsterdam UMC (Netherlands). IHC: Immunohistochemistry; ISH: In situ hybridization. Map created with mapchart.net. Figure created with BioRender.com

### Study design

#### LEGACy part 1

**LEGACy part 1** is a case control study focused on identifying geographic variations in known and potential risk factors including detailed food consumption habits, BMI, socioeconomic status, smoking and alcohol use and family history of cancer. Within the study, cases are defined as adults with histologically confirmation of stage I-IV gastric adenocarcinoma (including GEJ cancer) within 6 months prior to inclusion, while controls are patients without gastric cancer from the same geographic regions as the cases, undergoing gastroscopy to rule out malignant disease. After signing informed consent forms, participants will be called by a trained member of the local LEGACy team who will record responses to the 30 min questionnaire in the eCRF. Epidemiologic data will be collected through a questionnaire. This questionnaire was modified and adapted according to the populations epidemiological facts of these regions to a shorter version to make a feasible approach in a 30 min call, including the most representative variables to measure and compare risk factors associated in EU and LATAM populations. A list of the parameters is provided in supplement 2. The data on risk factors will be compared between the different geographic regions and correlated with corresponding clinical data including age, sex, histology, disease stage and outcomes. Each recruiting center will include 100 cases and 100 control patients for the questionnaire, resulting in a total recruitment of 800 cases and 800 controls. Patients of this study are allowed to participate in other LEGACy studies when meeting all inclusion criteria as shown in Fig. 2.

**Fig. 2 Fig2:**
[figure not shown]
Subjects, inclusion criteria (IC) and exclusion criteria (EC) for three sub-studies of the LEGACy project. (YO: years old; ICS: Informed consent sheet; GC: gastric cancer; GEJ: gastro-esophageal junction cancer; w/o: without)

#### LEGACy part 2

**LEGACy part 2** is a tumor tissue sampling study focusing on multi-omics characterization of advanced GC in EU and LATAM populations. Data analyses include immunohistochemistry (IPATIMUP and GENPAT), genomics (VHIO and PUC), the immunome (VUMC and INCAN) and microbiome (IPATIMUP and PUC) of which the details can be found in Fig. 1. The patient population targeted of this study are treatment-naive advanced (stage III-IV) GC or GEJ adenocarcinomas. Subjects with gastroscopy indicated for a benign disease and confirmed absent of GC will be invited to participate as study controls.

From each patient included as a case eight tumor biopsies will be collected in formalin during gastroscopy, and in case of surgical tumor removal the resection specimen can be used as substitute. In cases, additional biopsies will be collected from non-tumoral gastric mucosa areas within four cm (2 in formalin, 1 snap frozen) and more than four cm around the tumor (2 in formalin). For controls, biopsies will be collected from gastric mucosa tissue at the corpus (2), antrum (2), and incisura (1) in formalin, and one extra antrum biopsy will be snap frozen in liquid nitrogen. For microbiome analysis, one of the gastric mucosa biopsies from each patient will be snap frozen in liquid nitrogen. Blood samples will be collected in one serum and 2 EDTA tubes of 6-10 ml each at the time of gastroscopy to isolate plasma, serum and non-viable peripheral blood mononuclear cells from both cases as controls. The biopsies collected and fixed in formalin will be paraffin-embedded (FFPE). All sample collections will be done in a standardized matter following a uniform lab manual. All FFPE tissues will be centrally collected at one destinated center, subjected to pathological examination by an expert pathologist and then distributed for further analyses. QC on each sample before and after RNA and DNA extraction will be performed, according to the different protocol requirements by the expert centers who perform the multi-omic determinations as indicated in Fig. 1.

Our first aim is to identify potential molecular subgroups that can be attributed to existing clinically relevant classification models, such as the TCGA molecular subgroups. Patients will therefore be stratified into subgroups based on the multi-omic variables that have tumor-driving potential and are distinctive for each specific subgroup. These features will be correlated with their corresponding clinical, pathological, and epidemiological characteristics. As a multi-omics method is not economically or practically applicable in clinical setting, a final cost-effective set of the most clinically relevant biomarkers will be proposed for validation in clinical practice.

The first half of the patients will be considered as training cohort. After analyzing the results of this cohort, the most relevant molecular biomarkers will be converted into more cost-effective panels and validated in the second half of the patients: the validation cohort. Based on GC incidence and presentation of advanced GC at each participating center in this proposal for the duration of 3 to 4 years it was decided to include 50 cases and 50 controls of each center (total 400 cases and 400 controls).

### LEGACy part 3

This study consists of an online module for recording the knowledge of the general population on GC risk factors and symptoms and to provide education, as certain populations are reported to have low knowledge on risk factors [23]. The strategy is organized as follows: a) The participants consent their participation through an online informed consent form. b) The participants complete an online questionnaire on their knowledge of gastric cancer risk factors and symptoms and this information is recorded for further analysis by the LEGACy group. c) After completing the questionnaire, the subjects receive an informational brochure and a short video containing essential information about GC. d) After that, the same online questionnaire is provided after a few months to record the short- and long-term impact of this educational approach. The questionnaire lasts 15 minutes and was prepared by the LEGACy consortium partners and validated by the European Cancer Patient Coalition organization. The questionnaire and video is available in English, Spanish, Portuguese and Dutch. Finally, throughout this study, knowledge and best practices will be shared though educational training programs to share members’ expertise and train all involved project members. The courses will cover different aspects of GC including epidemiology, pathology, diagnosis, current and future treatments. Moreover, open access links to the online training courses are disseminated through the LEGACy website and social media channels to reach anyone interested to learn more about gastric cancer, to make a continuous and durable impact in GC research and clinical management.

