### Sample size considerations

Since there are a large number of specific factors to be analyzed with multiple techniques, and this is mostly a descriptive study, formal sample size calculations for the study as a whole were not feasible. The number of patients to include in the studies was decided upon from the following considerations:(i)LEGACy part 1, 2 and 3 study sample size was based on the participating clinical centers capacity of recruitment along the project.(ii)To get a better idea what sample size would be needed to give relevant results, we made an example calculation based on a RNA experiment in the two main groups. For example, we are planning to identify differential gene expression between two groups. Prior data indicates that the minimum average read counts among the differential genes in the control group is 5, the maximum dispersion is 0.5, and the ratio of the geometric mean of normalization factors is 1. Suppose that the total number of genes for testing is 20,000 and the top 100 genes are differentially expressed. If the desired minimum fold change is 1.5, we will need to study 200 subjects in each group to be able to reject the null hypothesis that the population means of the two groups are equal with probability (power) 0.8 using exact test. The FDR associated with this test of this null hypothesis is 0.01.(iii)Based on (i) and the calculation in (ii) it was decided to include 200 cases and 200 controls for the training cohort, and to add another 200 cases and 200 controls for the validation cohort in LEGACy part 2 to be sure the generated results would be usable.(iv)LEGACy part 1 is not limited to GC stage of disease. Therefore, it was decided to include two times the amount of patients included in part 2.

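### LEGACy part 2 allows resection specimens in cases only, so a pooled tumour-versus-control comparison mixes specimen type with disease; give biopsies precedence and check markers in biopsies alone

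*Protocol article*

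**What the plan says.** The section on LEGACy part 2 (Methods/design, Study design) sets the tissue rules.

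- **Case tumour samples.** The default is endoscopic: "From each patient included as a case eight tumor biopsies will be collected in formalin during gastroscopy". The same sentence then allows an exception: "in case of surgical tumor removal the resection specimen can be used as substitute". It does not say which specimen is used when both exist.
- **Case non-tumoral mucosa.** "additional biopsies will be collected from non-tumoral gastric mucosa areas within four cm (2 in formalin, 1 snap frozen"), with further biopsies taken farther from the tumour. No substitution is stated here.
- **Controls.** "For controls, biopsies will be collected from gastric mucosa tissue at the corpus (2), antrum (2), and incisura (1) in formalin", plus one snap-frozen antrum biopsy. All are endoscopic.

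The first half of patients is the training cohort and the second half the validation cohort. Under Sample size considerations, the worked RNA example compares two groups and concludes that "we will need to study 200 subjects in each group". Each half then has 200 cases and 200 controls.

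**The concern.** A surgical specimen and an endoscopic biopsy differ in how the tissue is obtained and handled before it reaches the laboratory, and molecular measurements may respond to that. Under the stated rule, such a difference can enter the case arm and never the control arm. If all tumour samples are pooled, a marker that reflects specimen handling can look like a marker of disease.

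The planned split into training and validation halves is the main protection against false leads. It guards against chance findings. It does not guard against a systematic difference produced by a collection rule common to both halves. Standardised collection, central pathology and quality control before and after extraction address quality within a specimen type, but do not remove a difference between types that exists only among cases.

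**Working it through.** **Inputs from the article (Sample size considerations).** "the minimum average read counts among the differential genes in the control group is 5, the maximum dispersion is 0.5"; 20,000 genes tested, 100 of them differentially expressed; fold change 1.5; power 0.8; FDR 0.01; 200 per group.

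**Inputs assumed, because the article gives none.** Resection share r among cases: 10-30%. Specimen effect d: 0.5-1 SD.

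**Step 1. Reproduce the article's figure.** The FDR converts to a per-gene level of

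alpha = 100 × 0.8 × 0.01 / (19,900 × 0.99) = 4.06e-5, two-sided z = 4.104.

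The article names an exact test; a Wald approximation on the log ratio of negative-binomial means gives

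n = (4.104 + 0.842)² × (1/5 + 1/7.5 + 2 × 0.5) / (ln 1.5)² = 24.46 × 1.333 / 0.1644 = 198.4 per group.

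This agrees with the stated 200.

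**Step 2. Size of the mixing.** If a marker has no true case-control difference, the pooled difference is r × d. It runs from 0.10 × 0.5 = 0.05 SD to 0.30 × 1 = 0.30 SD. With 200 against 200, the noncentrality is r × d × √100, that is 0.5 to 3.0.

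| r | d (SD) | Difference (SD) | Rejection at 5% | Rejection at 4.06e-5 |
|---|---|---|---|---|
| 0.10 | 0.5 | 0.05 | 8% | 0.02% |
| 0.10 | 1.0 | 0.10 | 17% | 0.1% |
| 0.20 | 1.0 | 0.20 | 52% | 1.8% |
| 0.30 | 0.5 | 0.15 | 32% | 0.5% |
| 0.30 | 1.0 | 0.30 | 85% | 13% |

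Allowing for the extra variance from mixing two specimen types lowers the top entries slightly, to 81% and 11%.

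**Step 3. Can it be separated?** Fit y = b0 + b1 × case + b2 × resection. There are three groups and three coefficients:

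- b0 = mean of controls
- b0 + b1 = mean of biopsied cases
- b0 + b1 + b2 = mean of resected cases

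Hence b1 = mean of biopsied cases minus mean of controls. The design matrix has full rank as long as some cases have biopsies. In simulations with a 1.5-fold specimen effect and no disease effect, the unadjusted log difference was about 0.04, 0.12 and 0.20 at 10%, 30% and 50% resections (in theory r × ln 1.5), and about 0.00 after adding the specimen term. Separation failed only when every case was a resection. Restriction to biopsies and adjustment for specimen type thus give the same case-control estimate, and resected cases add nothing to it.

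**Step 4. Price of separation.** Power with 200 controls and m biopsied cases, at the level in Step 1, is Φ(ln 1.5 / √(0.7/200 + 0.633/m) − 4.104), where 0.7 = 1/5 + 0.5 and 0.633 = 1/7.5 + 0.5.

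| Biopsied cases m | Power |
|---|---|
| 200 | 0.81 |
| 180 | 0.77 |
| 160 | 0.72 |
| 140 | 0.66 |

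**The case against.** A reader might infer that specimen type cannot be adjusted away because no control has a resection. The documents do not support that. Biopsy is the default in cases, so the effect is estimable (Step 3); the absence of resected controls costs precision, not identifiability. Restriction and adjustment do leave an estimate that describes biopsied cases. Applying it to all cases assumes that biopsied and resected cases are otherwise comparable.

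A reader might also infer a biased comparison of stage III with stage IV. The population is defined as "The patient population targeted of this study are treatment-naive advanced (stage III-IV) GC or GEJ adenocarcinomas", and the plan for the features is only that "These features will be correlated with their corresponding clinical, pathological, and epidemiological characteristics". No stage contrast is named, no resection rate by stage or region is given, and nothing ties resection to stage. Such correlations could be affected if resection differs by stage or region. Within cases, an ordinary covariate handles this wherever both specimen types occur at each level.

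The remaining objections stand in part:

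- The 5% rejection rates overstate the harm for the RNA screen, where the article's own FDR implies a far stricter level. The threshold for the other assays is not stated, so both columns are shown.
- The RNA calculation is called an example, recruitment capacity also set the sample size, and no rule for selecting markers from a case-control test is given.
- Tumour and control mucosa differ as tissues however they are collected. Non-tumoral biopsies from cases still allow a biopsy-to-biopsy comparison with controls, because the substitution is stated only for tumour samples.
- Replication of an artefact in the second half is not certain; it depends on similar resection shares in both halves, which the article does not state.
- The laboratory handbook, lab manual or full analysis plan may already record specimen type and set precedence. Their absence from a condensed article is not a fault. The point rests on the substitution rule that the article does state.

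**Conclusion.** The point holds as a modest design weakness with a cheap remedy. A pooled case-control comparison of tumour samples carries a specimen component equal to resection share times specimen effect, and validation under the same collection rule cannot be relied on to reveal it. Under the assumed ranges the component is 0.05-0.30 SD; what that means for false selection depends heavily on the threshold, from about 8-85% at a nominal 5% level to about 0.02-13% at the FDR-implied level. These figures rest on an assumed share and effect and apply only to markers that respond to specimen type. The component can be removed, with the separated contrast informed by biopsied cases alone. Nothing in the article is contradictory, and permitting a substitute specimen is a reasonable feasibility choice.

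**What to change.** 1. State in the part 2 collection rule that endoscopic biopsies take precedence as the analysed tumour sample whenever both types exist.
2. Record specimen type for every sample.
3. Let a marker chosen on a case-control difference enter the panel only if the difference keeps its direction and approximate size in a biopsy-only or specimen-adjusted analysis.
4. Include specimen type as a covariate in within-case analyses, including correlations with stage or region.

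The cost is one data field and one additional analysis. No patient is lost and resections remain usable within cases. The downside is lower precision in the check, as shown in Step 4. The stated RNA example leaves almost no margin (198.4 needed against 200 planned). The check should therefore be read for consistency of direction and size, without requiring significance, and the analysis of all cases can remain the main test.

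### Part 3 has one group, asked the same questions before and after the education, so the change in score cannot on its own be read as the impact of the brochure and video

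*Protocol article*

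**What the plan says.** The section LEGACy part 3 of the Protocol article sets out one sequence. After online consent, "The participants complete an online questionnaire on their knowledge of gastric cancer risk factors and symptoms". Next, "After completing the questionnaire, the subjects receive an informational brochure and a short video containing essential information about GC". Finally, "the same online questionnaire is provided after a few months to record the short- and long-term impact of this educational approach". The text describes no group without education, no group with delayed education, no group questioned only afterwards, and no second set of items.

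The same section says of separate teaching material that "open access links to the online training courses are disseminated through the LEGACy website and social media channels".

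The Abstract (Methods) gives the purpose of Part 3 as "to test and disseminate knowledge on GC risk factors and symptoms by a questionnaire and informative video" and draws its subjects from the general public. It calls Parts 1 and 2 case-control studies, but names no controls for Part 3. Under Sample size considerations, "LEGACy part 1, 2 and 3 study sample size was based on the participating clinical centers capacity of recruitment along the project", and the project is characterised by the phrase "this is mostly a descriptive study". No number of participants, effect size or test is given for Part 3. The limitations in the Discussion cover multi-site data and extrapolation to other countries only.

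**The concern.** The last step gives the repeat questionnaire a causal purpose, namely to show what the education achieved. The design yields only a before-after difference in people who chose to come back. Three other things can move that difference:

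- The first questionnaire shows participants the items and alerts them to the topic. They may remember the items or look them up.
- Information about gastric cancer can reach them from other sources during the months between the two rounds.
- Those who return may differ from those who do not.

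If the plan is followed as written, Part 3 could report an educational impact that its data cannot establish. No later analysis plan can recover a comparison that was never collected, so this is not a detail that an article simply leaves to a fuller document.

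**Working it through.** There is no Part 3 figure to reproduce. The worked sample size example in the article concerns an RNA comparison and supports Part 2. The check is therefore of what the design can identify, followed by an illustration.

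**1. What the observed change contains.** Let E be the effect of the brochure and video, R the effect of having met the same questions before, O outside information gained in the interval, and S the shift from selective return. Then

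observed change = E + R + O + S.

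There is one equation and four unknowns. Further follow-up rounds in the same group add equations but also new values of R, O and S, so E stays unidentified.

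**2. Direction.** R and O would normally raise scores. A gap of months may weaken recall of items (smaller R) while leaving more time for outside information (larger O). S can have either sign. If those who learned most return, it inflates the change. If those who already knew most return and have little left to gain, it deflates it. The net sign is not determined by the document.

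**3. Size, illustration only (all inputs assumed).** Take E = 0.3 SD, R + O from 0 to 0.3 SD, and S = 0.

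| R + O (SD) | Observed change (SD) | Excess over E |
|---|---|---|
| 0 | 0.3 | 0% |
| 0.1 | 0.3 + 0.1 = 0.4 | 0.1/0.3 = 33% |
| 0.3 | 0.3 + 0.3 = 0.6 | 0.3/0.3 = 100% |

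**4. Sample size does not help (all inputs assumed).** Suppose E = 0, S = 0 and scores rise by g SD through R + O. With pre-post correlation ρ, the SD of the change is s = √(2(1 − ρ)). A two-sided 5% paired z-test is significant with probability

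Φ(g√n/s − 1.96) + Φ(−g√n/s − 1.96).

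For ρ = 0.5, s = 1. With g = 0.2 and n = 200, g√n = 2.828, and Φ(0.868) = 0.81. Other values:

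| g (SD) | n = 100 | n = 200 | n = 400 |
|---|---|---|---|
| 0.1 | 0.17 | 0.29 | 0.52 |
| 0.2 | 0.52 | 0.81 | 0.98 |
| 0.3 | 0.85 | 0.99 | >0.99 |

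With ρ = 0.7 the probabilities are higher (for g = 0.2: 0.73, 0.955 and 0.999). If such a gain exists, a larger sample makes a false attribution more likely. The article states no test for Part 3, so this shows only what a conventional paired test would do.

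**5. What the available comparisons would remove.**

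- *Follow-up scores against baseline scores of people newly enrolling in the same calendar period.* Newcomers carry whatever background information has reached the public by then, so that part of O cancels. R remains. So do selective return and any difference in the kind of person enrolling, apart from what adjustment removes.
- *A random branch that skips the first questionnaire.* The difference in follow-up scores between branches estimates R, provided that return is similar in both. It does nothing about O: the unquizzed branch's follow-up score minus an earlier baseline score is still E + O plus any selection.

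**The case against.** The strongest reply is that impact is not what Part 3 is mainly for. The section opens with recording public knowledge and providing education, and the sample size section says "this is mostly a descriptive study". Much of this stands. Impact is one purpose among several, and a plain description of change would be acceptable. But the phrase on descriptive character explains why no formal sample size was calculated. It does not withdraw the reading that the Part 3 section gives to the repeat questionnaire.

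Secondly, the questionnaire can be seen as part of the educational approach, since the Abstract names it together with the video: "to test and disseminate knowledge on GC risk factors and symptoms by a questionnaire and informative video". On that reading, interest stirred by the first round belongs to the effect. This is arguable, and it would shrink the retest component of the problem. Outside information and selective return would remain.

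Thirdly, the evidence for outside information is thin. The links publicised on the website and social media lead to training courses, and nothing shows that Part 3 participants take them between rounds. That stands: outside information is possible, not demonstrated.

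A reader might go further and infer that Part 3 will overstate the effect, by 33% to 100%, and that only a randomised redesign can cure it. The documents do not support this. They give no retest gain, return rate or effect size, and the percentages come from assumed inputs. The random branch isolates the retest effect only, still compares self-selected returners, and adds randomisation to a study described as observational.

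**Conclusion.** The point holds as a limit on interpretation. Part 3 as described is an uncontrolled before-after study with identical items, and its change score cannot by itself carry the stated conclusion about impact. The size and net direction of the bias are unknown from the document. Under the assumed inputs above, the excess runs from none to a doubling, before selective return.

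The conclusion rests on two assumptions. First, no comparison group exists: this is inferred from the sequence described, since Fig. 2 is not shown, but nothing in the text suggests one. Second, the result will be reported as the section words it. The recording and teaching purposes of Part 3 are unaffected.

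**What to change.** - **LEGACy part 3:** replace the stated purpose of the repeat questionnaire, to record short- and long-term impact, with: *to describe the change in knowledge score among participants who return*.
- **Discussion, limitations:** add that Part 3 is uncontrolled, and that its change scores may reflect repeated questioning, outside information and selective return as well as the education.
- **Analysis:** compare baseline scores of returners and non-returners. This assumes that a person's two questionnaires can be linked.
- **While enrolment continues:** also compare follow-up scores with baseline scores of people newly enrolling in the same calendar period, adjusted for country, language and other recorded characteristics. This uses data already being collected and accounts for background information. State that it does not remove the retest effect.

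The cost is a weaker stated conclusion and a little more analysis.

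A random branch that sends some entrants straight from consent to the brochure and video is optional. It would isolate the retest effect only, needs an ethics amendment, and loses baseline answers from those entrants.
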